## 3. Methods

### 3.1. Study Design

This study is a double-blind, parallel, 1:1 randomized controlled trial (RCT). After enrollment assessments, participants will be randomly assigned to either the experimental group, receiving the interactive podcast program, “Living with Type 1 Diabetes to Grown-Up,” or the active control group, receiving a sham treatment using an ineffective e-book, “Transitioning from Adolescence to Early Adulthood: The Ins and Outs of Type 1 Diabetes” which will be given at enrollment [57]. Both interventions will last for 3 months. Outcome measures will be evaluated at four time points: pre-randomization (T0), immediately postintervention (T1), 3 months post-intervention (T2), and 6 months postintervention (T3). This study has been registered at ClinicalTrials.gov (under identifier NCT06464640).  Figure 2 shows the detailed study process.

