#### 3.3.2. Sample Size Calculation

Few studies have explored podcast-based interventions for chronic diseases or illnesses in adolescents. As podcasting is a technology-based intervention method, results from our prior study of Healthcare CEO App [57] were used for sample size calculation. Effect sizes were calculated using Cohen's *d*. For groups of 19 participants each, the mean HbA1c for the experimental vs control group at 3, 6, and 9 months postintervention was 7.93 ± 1.36 versus 8.69 ± 2.40, 8.30 ± 1.29 versus 8.82 ± 2.69, and 8.24 ± 1.58 versus 8.87 ± 2.72, respectively, yielding an effect size of 0.38, 0.26, and 0.32, respectively.

Using G-Power 3.1.9.4 software, the required sample sizes were calculated for each group across the three time points as 18, 38, and 26 participants, respectively. Assumptions included two groups with four repeated measures, *α* set at 0.05, power at 0.80, and a correlation coefficient of 0.5. No participants withdrew from our prior study [57]. However, considering a conservative dropout rate of 12% based on similar online intervention studies with a 6-month follow-up period [64], the number of participants was increased to 21, 44, and 30 per group. The maximum sample size calculated based on the smallest effect size at T2 was chosen. Therefore, the total sample size will be 88 participants.

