### 3.8. Statistical Analysis

Descriptive statistics such as frequency distribution, percentage, mean, standard deviation, and maximum/minimum scores will be utilized to characterize the subjects' demographics, disease characteristics, outcome variables at enrollment, and podcast usage. The efficacy of the intervention will be assessed using generalized estimating equation (GEE) modeling, which accommodates repeated measurements and deals with missing data effectively, following the intention-to-treat principle.

GEE will evaluate differences in outcome variables between experimental and control groups over time. Linear GEE models will be applied for all the continuous outcomes. The models will include fixed effects for the group (experimental vs. control), time (baseline, postintervention, and 3 and 6 months postintervention), and their interaction. The working correlation structure will be selected based on the quasi-likelihood under the independence model criterion [77]. Statistical significance will be determined at *p* < 0.05. All analyses will be conducted using IBM SPSS 26.0 for Windows.

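### The 80% power in 3.3.2 fits a group difference averaged over T0–T3 with the full effect already present at pre-randomization T0, not the group-by-time effects of the planned GEE

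*Protocol article*

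**What the plan says.** Section 3.3.2 takes three HbA1c effect sizes from the sponsor's prior app study, 0.38, 0.26 and 0.32, labelled as Cohen's d. Each is a between-group difference at a single visit. The inputs to the software are given as "Assumptions included two groups with four repeated measures, *α* set at 0.05, power at 0.80, and a correlation coefficient of 0.5". The results are 18, 38 and 26 per group. The final choice is explained by "The maximum sample size calculated based on the smallest effect size at T2 was chosen", which gives 38 per group, 44 after 12% dropout, and 88 in total. The G*Power routine is not named.

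Section 3.1 shows that one of the four measures precedes randomization: "Outcome measures will be evaluated at four time points: pre-randomization (T0), immediately postintervention (T1), 3 months post-intervention (T2), and 6 months postintervention (T3".

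Section 3.8 specifies linear GEE for outcomes on a continuous scale: "The models will include fixed effects for the group (experimental vs. control), time (baseline, postintervention, and 3 and 6 months postintervention), and their interaction". It does not single out one contrast or visit as the main HbA1c test.

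**The concern.** A power figure describes one test under one alternative. The four-measure calculation appears to test one group difference averaged over T0 to T3, with the same effect at every visit. Randomization makes the expected difference at T0 zero. In the planned GEE, where baseline is a level of time, the treatment effect is the change in the group difference from T0, which is a group-by-time term. The effect entered was moreover a single-visit difference, yet it was given the precision of a four-visit average.

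The two tests respond to different patterns. If the group difference were equal at all four visits, which is the alternative the sizing routine assumes, every group-by-time contrast would be zero and would reject only 5% of the time.

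At stake is whether 80% can be read as the chance that the planned analysis detects the planning effect. The same question would remain if the d/f entry error, a separate point, were corrected by re-running the same routine.

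**Working it through.** **Inputs.** From 3.3.2: two groups, m = 4, α = 0.05, power 0.80, r = 0.5, effects 0.38, 0.26 and 0.32, and 38 per group before dropout. From 3.1: T0 is pre-randomization. Assumed here: two-sided tests, unit SD in both arms, compound symmetry, zero effect at T0 and an equal effect d at T1–T3. The value r = 0.7 is also assumed, to show sensitivity.

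**Step 1: reproduce the plan's figures.** For the between-factors routine, λ = N·f²·m / [1 + (m − 1)r], with 1 and N − 2 df. With m = 4 and r = 0.5 the multiplier is 4/2.5 = 1.6.
- For f = 0.26 and N = 76: λ = 76 × 0.0676 × 1.6 = 8.22, power 80.8%. At 37 per group power is 79.7%, so 38 is the smallest.
- For 0.38, 0.26 and 0.32 the routine gives 18, 38 and 25 per group, against the stated 18, 38 and 26.
- Dropout: 38/0.88 = 43.2, so 44 per group and 88 in total, as stated.

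Alternatives tried:
- within-between interaction routine: 6, 11, 8 with the effects entered as f; 20, 41, 28 with f = d/2;
- between factors with three measures: 20, 40, 27;
- two-sample t test: 110, 234, 155.

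None matches as closely. The match requires 0.26 to be read as f, which for two equal groups means d = 2f = 0.52.

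**Step 2: power of the planned type of test.** With n per arm:
- T2 minus T0: variance 4(1 − r)/n. At n = 38 and r = 0.5 the SE is √(2/38) = 0.229. For d = 0.52 the noncentrality is 0.52/0.229 = 2.27, power 61%.
- Mean of T1–T3 minus T0: variance (2/n)(4/3)(1 − r). The SE is √0.0351 = 0.187, noncentrality 2.78, power 78%.
- Joint interaction (3 df): with equal effects at T1–T3, λ = 3n·d²/[8(1 − r)] = 114 × 0.2704/4 = 7.71, power 64%.
- Four-visit average with zero effect at T0: effect 0.75 × 0.52 = 0.39, SE √[(2/38)(2.5/4)] = 0.181, noncentrality 2.15, power 57%.

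The one-df contrasts use the noncentral t with 74 df, and the joint test the noncentral chi-square. The same formulas give, at 38 per arm:

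| Test | d = 0.52, r = 0.5 | d = 0.52, r = 0.7 | d = 0.26, r = 0.5 | d = 0.26, r = 0.7 |
|---|---|---|---|---|
| Sizing routine (full effect at T0 too) | 81% | 72% | 29% | 25% |
| T2 minus T0 | 61% | 82% | 20% | 30% |
| Joint 3-df interaction | 64% | 87% | 19% | 29% |
| T1–T3 average minus T0 | 78% | 94% | 28% | 42% |

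**Step 3: does the d/f correction alone repair it?** With f = 0.13, the routine reaches 80% at N = 294 (λ = 294 × 0.0169 × 1.6 = 7.95). At 147 per arm, d = 0.26 and r = 0.5:
- T2 minus T0: noncentrality 0.26/√(2/147) = 2.23, power 60%.
- Joint test: λ = 441 × 0.0676/4 = 7.45, power 62%.
- T1–T3 average minus T0: noncentrality √7.45 = 2.73, power 78%.

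**The case against.** **The routine is inferred.** Section 3.3.2 does not name it, and the interaction routine with f = d/2 comes fairly near (20, 41, 28). This stands as a caution. The between-factors routine fits all three figures within one and no variant tried fits as well, so the identification is probable but not documented.

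**The direction is not fixed.** A reader might infer that the mismatch always overstates power. The calculations do not support that. At r = 0.5 the T1–T3 average minus T0 has 78% against the routine's 81%, a loss of 3 points. At r = 0.7 all three group-by-time tests exceed the routine. This stands in full. It limits the claim about size but does not make 80% the power of the planned analysis. At the protocol's own r = 0.5, two of the three tests fall well short.

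**The larger shortfalls use d = 0.52, which the protocol does not claim.** That is true: the text labels 0.26 as Cohen's d. The 0.52 case only isolates this point from the d/f error. At d = 0.26 the gap from the routine is 1 to 10 points on a base of 29%, and the d/f error is the larger problem.

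**The assumptions lean low.** With the stated pattern 0.38/0.26/0.32 at T1–T3, the joint test has 29% rather than 19% at 38 per arm. GEE also uses partial data. With all 44 per arm complete, large-sample figures for d = 0.52 are 68% (T2), 71% (joint) and 85% (average). These soften the numbers without changing the conclusion.

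**The main contrast may be in an SAP.** It may, and its absence from 3.8 is not the fault raised here. The power sentence in 3.3.2 is printed now and must describe whichever contrast is chosen.

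**Conclusion.** The power statement in 3.3.2 is wrong as written. Its figures match a test that averages over T0–T3 and places a full effect at pre-randomization T0, while the analysis in 3.8 carries the treatment effect in the group-by-time terms. At r = 0.5, 38 evaluable per arm, equal effect at T1–T3 and none at T0, power lies between 61% and 78% at the effect the software read, and between 19% and 28% at the effect the protocol labels.

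Two stronger readings are not supported. The documents do not show that this mismatch by itself leaves the trial underpowered, because the gap depends on the contrast and on r. Nor do they make the T1–T3 average the required main test: that is a choice of estimand, and 3.3.2 itself sized the trial on T2. The conclusion rests on an inferred routine and on compound symmetry, so confidence is moderate.

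**What to change.** In 3.3.2:
- state which G*Power routine was used;
- do not count T0 as a visit that carries a treatment effect;
- replace the power sentence with the power, at 38 evaluable per arm, of the group-by-time contrast that 3.8 names as the main HbA1c test, with the effect expressed as d = 0.26 and a short range of r.

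In 3.8, name that contrast. The T1–T3 average minus T0 is one efficient option: about 28% at r = 0.5 and 42% at r = 0.7. Its downside is that an effect confined to one visit is diluted. If T2 minus T0 is kept as the main test, state about 20% and 30%.

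Make this change together with the d/f correction. Re-running the same routine with f = 0.13 would print 80% at N = 294 while leaving about 60% for T2 minus T0 and 62% for the joint test at r = 0.5.

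The cost is wording in two sections, with no new data or visits, and a printed power well below 80%. Whether to keep 88 participants on that basis is a decision for the sponsor, to be taken with the d/f correction.

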### 3.4. Randomization and Blinding

A statistician not involved in data collection will use SPSS to randomly assign participants, with the results enclosed in sealed envelopes. After baseline assessment, envelopes will be opened, and group assignments (experimental or active control) will be disclosed to the interventionist via phone only.

Double blinding will be employed for data collectors and participants. Participants will be blinded through a sham treatment (see below), and data collectors will not have access to group assignments. To assess the effectiveness of the blinding, data collectors will be asked two questions at the start and conclusion of the study: “Are you aware of the interventions in this study?” and “Can you identify whether the participant was in the experimental or control group based on any clues?” Participants will also answer two questions: “What guidance did you receive during the study?” and “Do you think you were in the experimental or active control group?” These questions will help evaluate the success of the blinding process.

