### 3.2. Study Setting

Participants will be recruited from the pediatric and adult endocrinology outpatient clinics and wards of two medical centers in northern Taiwan specializing in youth T1D treatment. The combined annual patient pool at these centers includes approximately 350 eligible candidates. We anticipate approaching approximately four eligible patients per week, with an expected refusal rate of 20% following the COVID-19 pandemic to recruit 12–16 participants per month [57]. We aim to recruit 88 participants (as per the sample size calculation detailed below) within a maximum of 6–8 months. Should unforeseen challenges, such as another public health crisis, arise, we will extend the recruitment period or explore additional recruitment sites as contingency measures.

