### 3.3. Participants

#### 3.3.1. Eligibility Criteria

Participants will be recruited using convenience sampling. Inclusion criteria are as follows: (1) diagnosed with T1D by an endocrinologist before the age of 16, with a disease duration of more than 6 months, allowing sufficient time for diagnosis stabilization and self-care training [58, 59]; (2) aged between 16 and 25, representing the transition period from late adolescence to early adulthood [58, 60]; (3) mean HbA1c level ≥ 7.5% in the year before inclusion to identify patients who have inadequate blood sugar control, making them suitable candidates for the podcast intervention; (4) the ability to communicate in Mandarin or Taiwanese; (5) possession of a smartphone, tablet, or computer with Internet access, enabling program transmission and voice interaction for data collection; and (6) willingness to participate in the study with signed informed consent. For minors, the legal guardian must also provide signed informed consent. Individuals with other metabolic diseases, chromosomal abnormalities, major illnesses, or significant auditory and cognitive impairments will be excluded from this study, as these conditions may affect their healthcare needs and influence their understanding and utilization of the intervention [61, 62]. Participants using continuous glucose monitoring (CGM) will also be excluded from the trial, as its adoption remains low in Taiwan due to high out-of-pocket costs despite partial reimbursement [63]. This ensures consistency in glycemic data sources.

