#### 3.7.2. Primary Outcome: Wellbeing—Disease Control Outcomes

Assessed through HbA1c, the percentage of self-monitored blood glucose readings within the 70–180 mg/dL range, the number of hypoglycemic events (blood glucose < 70 mg/dL), and the number of hyperglycemic events (blood glucose > 180 mg/dL) [70] will be noted. HbA1c will be recorded from electronic medical records after blood samples are collected during patient visits. The percentage of self-monitored blood glucose readings within the 70–180 mg/dL range will be calculated using the formula: (number of values within the 70–180 mg/dL range/total number of tests)∗100% [57].

A data downloader at outpatient clinics will be used to retrieve the past 3 months' blood glucose data and reset it to prevent data from overlapping or being overwritten. Subsequently, two data collection assistants will simultaneously review the data manually. If discrepancies arise, the principal investigator will verify the data. Finally, interrater reliability will be assessed using Cohen's Kappa coefficient to ensure consistency in their evaluations [71]. In cases of abnormal blood glucose values, such as hypoglycemia, if the participant follows up with a blood glucose check 15 min after consuming carbohydrates, only the first recorded value (i.e., the pretreatment blood glucose value) will be used for analysis. Commercial blood glucose meters can store 500–1000 data points, and participants typically measure 2–5 times daily. Therefore, based on prior studies, data coverage is not expected to be an issue [57].

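### No blocking or stratification is described for an 88-participant two-center trial, and the HbA1c model has no baseline or center adjustment, although center and HbA1c are known before allocation

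*Protocol article*

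**What the plan says.** Section 3.4 gives the sequence generation as "A statistician not involved in data collection will use SPSS to randomly assign participants, with the results enclosed in sealed envelopes", and the order of events as "After baseline assessment, envelopes will be opened, and group assignments (experimental or active control) will be disclosed to the interventionist via phone only". Section 3.1 sets a 1:1 ratio and Section 3.3.2 sets 44 per group. None of these sections mentions blocks, strata, minimization or separate lists by center.

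On the population, Section 3.2 says "Participants will be recruited from the pediatric and adult endocrinology outpatient clinics and wards of two medical centers in northern Taiwan". Section 3.3.1 requires "mean HbA1c level ≥ 7.5% in the year before inclusion" and sets no upper limit. On the outcome, Section 3.7.2 says "HbA1c will be recorded from electronic medical records after blood samples are collected during patient visits".

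Section 3.8 specifies linear GEE models with fixed effects for group, time and group by time. Time has four levels, one of them baseline. No other covariate is named.

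**The concern.** Recruitment spans two centers and both pediatric and adult services. Entry HbA1c has a floor and no ceiling, and the prior trial's follow-up SDs run from 1.29 to 2.72. With 88 participants, the arms can differ by chance at baseline by as much as the effect the trial was sized on. Stratification reduces that at the design stage, and baseline adjustment handles it in the analysis. The article describes neither, although the data for both are in hand before allocation. At stake are the precision of the HbA1c comparison and how readily a result can be interpreted if the baseline table shows a visible gap.

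**Working it through.** **Inputs.** From Section 3.3.2: 44 per group; at the time point that sets the sample size, HbA1c 8.30 ± 1.29 versus 8.82 ± 2.69; correlation 0.5; 12% dropout. The baseline SD is not stated, so follow-up SDs from the prior trial stand in for it (an assumption).

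**The plan's own figures.** 38 / (1 − 0.12) = 43.2, rounded up to 44 per group, or 88 in total, as stated. The raw difference is 8.82 − 8.30 = 0.52 points. The root-mean-square SD is √[(1.29² + 2.69²)/2] = 2.11, so 0.52/2.11 = 0.25, close to the middle value in "yielding an effect size of 0.38, 0.26, and 0.32, respectively".

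**Chance of a baseline difference of 0.52 points or more, in either direction.** SE = SD × √(2/44) and P = 2 × [1 − Φ(0.52/SE)].

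| Assumed baseline SD | SE | P |
|---|---|---|
| 1.29 | 0.275 | 6% |
| 1.5 | 0.320 | 10% |
| 2.1 | 0.448 | 25% |
| 2.69 | 0.574 | 36% |

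These figures hold for any 44:44 allocation not balanced on HbA1c; blocking alone would not change them.

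**In SD units.** SE = √(2/44) = 0.213, so P(difference ≥ 0.26 SD) = 22%.

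**What the stated model does with an imbalance.** With baseline as a level of time, the treatment effect would be read from the interaction, which is a difference in change from baseline. Given a baseline difference D and correlation ρ, and no true effect:

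- the follow-up difference is expected to be ρD;
- the change difference is expected to be (ρ − 1)D, which is −0.5D at ρ = 0.5;
- the baseline-adjusted difference is expected to be 0.

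In simulation (44 per group, one follow-up, 20,000 trials per setting), trials with D of at least 0.26 SD had a mean D of 0.36 SD. The change contrast shifted by −0.18 SD and the follow-up-only contrast by +0.18 SD, while the adjusted contrast did not shift. The type I error of the change test was 5.2% over all trials and 11.1% among trials with an imbalance of at least 0.26 SD in either direction. For the baseline-adjusted test it was 5.5% among those trials. At ρ = 0.7 the change contrast shifted by −0.11 SD and its conditional error was 8.7%.

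**Precision.** In units of 2/n, the variance of the change contrast is 2(1 − ρ) = 1.00 and that of the adjusted contrast is 1 − ρ² = 0.75, a 25% reduction in theory. The simulated SDs of 0.2128 and 0.1853 give 1 − (0.1853/0.2128)² = 24%.

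**Gain from stratifying.**

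- Balancing on a median split of baseline HbA1c itself multiplies the variance of D by 1 − 2/π = 0.363, and P(difference ≥ 0.26 SD) falls from 22% to 4.3%.
- If prior-year mean HbA1c correlates 0.8 with baseline (an assumption), the factor is 1 − 0.637 × 0.64 = 0.592. At SD 2.1 the SE is 0.345, and the chance of a 0.52-point gap falls from 25% to 13%.
- The variance of the change contrast then falls from 0.75 + 0.25 = 1.00 to 0.75 + 0.25 × 0.592 = 0.898, about 10% (about 11% in simulation).
- Strata on center and clinic alone, explaining an assumed 2% to 20% of HbA1c variance, leave the 22% at 22% to 17%.

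**Center mix.** With two equal centers (an assumption) and 44 per arm, the arms differ by 20 or more percentage points in center mix in 5.4% of allocations.

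**The case against.** The strongest reply is that this is a journal article, which commonly leaves block sizes and strata to the full protocol. A reader might infer that the trial uses a single unstratified list. The article does not say so: a fixed 44:44 list, a blocked list or separate lists by center would all fit its wording. That stands, and the randomization part of this point is conditional for that reason. The model in Section 3.8, by contrast, is spelled out.

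Second, a reader might infer that a baseline gap passes straight into the result and can mimic or hide the effect. It does not. The interaction contrast subtracts the baseline difference, and the test's overall error rate already allows for chance imbalance. What remains at correlation 0.5 is about half the imbalance with its sign reversed, plus the loss of precision.

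Third, the 25% depends on an SD borrowed from follow-up data with very unequal arms; at an SD of 1.29 it is 6%. It also partly reflects how small the 0.26 planning effect is for a trial of this size. If 0.26 were Cohen's f rather than d (so d = 0.52), an imbalance as large as the effect would have a 1.5% chance. This stands, so the range must accompany the figure.

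Fourth, a reader might infer that the two centers' laboratories differ. No passage says this; Section 3.7.2 says only that values come from medical records.

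Fifth, simple assignment would give exactly 44:44 in only 8.5% of trials, but this matters little. At the edge of the 95% range (35 versus 53), the effective total is 4 × 35 × 53 / 88 = 84.3, a loss of about 4%.

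**Conclusion.** The point holds as one about efficiency and interpretability. It is not a validity failure: 1:1 randomization without strata is sound, and the planned test keeps its 5% level. As described, the plan leaves a 25% chance of a baseline HbA1c gap of at least 0.52 points at SD 2.1 (6% to 36% for SDs of 1.29 to 2.69), provided that allocation is not balanced on HbA1c. The stated model over-corrects for such a gap by about half of it at correlation 0.5.

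The firmest part is the missing baseline adjustment, worth about 24% of the variance of the treatment contrast at that correlation. Stratifying on prior-year HbA1c is a smaller, inexpensive gain of about 11% if the change contrast is kept. The documents do not support the stronger readings of a stated single unstratified list, a biased result or differing laboratories.

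**What to change.** **Section 3.4.** State that the statistician prepares the list in randomly permuted blocks of varying size, stratified by center and by two levels of prior-year mean HbA1c, with the cut fixed in advance near the clinics' expected median. Use sequentially numbered envelopes for each stratum, and withhold block sizes from the research assistants because the interventionist learns each allocation. If the full protocol already does this, say so in the article.

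**Section 3.8.** Analyze post-baseline HbA1c with baseline HbA1c as a covariate, together with group, time, group by time and center. Alternatively, keep baseline as an outcome and constrain the arms to a common baseline mean. That route adjusts only through the working correlation, so an independence structure must not be used with it. Adding only a stratum main effect to the current model is not enough: it is constant over time and cancels from the group-by-time contrast.

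**Cost.** One list program and four envelope sets (2 centers × 2 HbA1c levels), with a small risk of drawing from the wrong set. No extra data, visits or staff are needed and N stays 88. Section 5 plans recruitment from November 2024. If it has begun, the allocation of those already enrolled cannot be changed, but the model change still applies and should be fixed before outcomes are examined by arm.

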### 3.5. Intervention and Sham Treatments

#### 3.5.1. Experimental Group: Intervention

The intervention comprises the interactive podcast program, “Living with Type 1 Diabetes to Grown-Up,” which includes podcast episodes and interactive voice feedback. The program features 36 episodes, released at a rate of three per week over a 3-month intervention period [65]. Based on pilot testing for optimal duration and speech rate [56], each episode lasts 8–15 min with a word count of 160–220 words per minute. The content incorporates participant recommendations and uses appropriate language, presented lightly and engagingly. The topics and subtopics are detailed in Table 1. In addition to episode ratings and encouraged comments, participants will provide voice feedback aligned with the objectives and content of each unit to enhance practical application. During the first 9 weeks of the intervention, every 3 weeks (at Weeks 3, 6, and 9), participants will select a topic from the podcast episodes they have completed and provide voice feedback based on the PRIDE interactive voice feedback protocol and steps, as detailed in Table 2. The principal investigator will then coordinate expert responses tailored to participants' feedback, delivered in the following weeks 4, 7, and 10. Each participant will engage in three personalized voice feedback interactions over the study period, and all feedback will be thoroughly documented to assess TF through content checking, ensuring accurate implementation and alignment with participant needs. While episodes cannot be downloaded, participants can listen to them again throughout the intervention.

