#### 3.5.2. Active Control Group: Sham Treatment

Our previous study demonstrated that e-books did not have a significant impact on glycemic control (HbA1c: 8.30 ± 1.29 vs. 8.82 ± 2.69, *p* = 0.477), diabetes knowledge (16.59 ± 3.26 vs. 15.42 ± 3.85, *p* = 0.336), self-care behaviors (152.94 ± 13.38 vs. 155.95 ± 14.56, *p* = 0.525), self-management confidence (29.82 ± 4.30 vs. 27.63 ± 5.82, *p* = 0.212), or interpersonal distress (11.00 ± 5.01 vs. 10.53 ± 6.54, *p* = 0.811) after 6 months in our prior trial [57]. Therefore, the active control group will receive the e-book “Transitioning from Adolescence to Early Adulthood: The Ins and Outs of Type 1 Diabetes,” compiled from the Healthcare CEO app collection, as a sham treatment. This title and content indicate its suitability as a minimally active control that is thematically relevant [66, 67]. The topics in the e-book include (1) diabetes knowledge, (2) how to manage your blood sugar, (3) eating and exercising well, (4) healthy interpersonal relationships, (5) parent–child harmony, and (6) you are not alone. Each unit includes recommended readings, such as “Needles” and “My Life Is Not Controlled by Diabetes.” Although parts of the themes are similar, the e-book is simplified to 600–800 words of pure text per unit, lacking T1D patient experience sharing and interactive engagement. Participants in the active control group will not be reminded to read the e-book, no additional interventions or consultations will be provided, and no follow-up calls will be made during the intervention. After the study, participants in the active control group will be offered the opportunity to listen to all podcast episodes and receive the same incentives as the experimental group, if desired. The intervention characteristics of the experimental and active control groups are presented in Table 3.

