## 4. Discussion

### 4.1. Strengths

This study will evaluate the efficacy of the interactive podcast program “Living with Type 1 Diabetes to Grown-Up” using a double-blind, parallel 1:1 RCT. The program has several strengths. First, its development is theory-based [51] and tailored to the healthcare needs of T1D patients in transition [14, 17], employing a user-centered approach for evaluation and testing [53–55]. The content, number of episodes, frequency, duration, and language are all designed to meet patients' expectations during this transition [56]. Second, the program's immediate personalized interaction through voice feedback enhances information exchange by avoiding traditional text or photo communication. This voice messaging approach improves content review, applicability to daily life, and professional support, increasing patients' motivation and willingness to engage [79]. This feature sets the program apart from existing podcasts, audiobooks, or certain YouTube content. Finally, TF is a significant factor affecting the efficacy of RCTs [80]. Therefore, both the experimental and control groups will implement methods to standardize treatments received and optimize TF, enhancing the credibility of the study findings [80]. Furthermore, in addition to the rigorous RCT design, this study has developed strategies to enhance TF based on existing literature and increased the number of research assistants. Comprehensive classroom and clinical shadowing training will ensure effective TF monitoring (File S1). These strategies allow for a more comprehensive analysis of the intervention's efficacy and help reduce bias in the study results.

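### The trial is labelled double-blind, but participants know which material they receive and can at most be masked to the study hypothesis

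*Protocol article*

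**What the plan says.** Section 3.1 describes the trial as double-blind. Section 3.4 names who is blinded and how: "Double blinding will be employed for data collectors and participants", and then "Participants will be blinded through a sham treatment (see below), and data collectors will not have access to group assignments". Section 4.1 repeats the description: "using a double-blind, parallel 1:1 RCT".

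The arms are set out in Section 3.5 and Table 3. For the experimental arm, "The program features 36 episodes, released at a rate of three per week over a 3-month intervention period". Section 3.5.1 adds three personalised voice feedback exchanges with expert replies. Section 3.6.1 adds a Wednesday reminder when backend data show that episodes were not heard. Table 3 lists a phone contact at 1.5 months for this arm only.

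The control e-book is plain text of 600–800 words per unit, with no interactive element. Section 3.5.2 states: "Participants in the active control group will not be reminded to read the e-book, no additional interventions or consultations will be provided". It also excludes follow-up calls during the intervention.

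Section 3.4 plans a check of blinding. Participants are asked, among other things, "Do you think you were in the experimental or active control group". The limitations in Section 4.2 mention neither imperfect participant blinding nor expectation bias.

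**The concern.** A sham hides the treatment itself only if it resembles that treatment. Here the recipient can see or hear the difference: audio or text, exchange or none, prompts or none. What could remain hidden is which of the two products the investigators expect to work better. That is masking to the hypothesis, a weaker property than participant blinding, and the article does not describe it that way.

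The distinction matters most for the self-rated secondary outcomes. Sections 3.7 and 3.7.3 to 3.7.5 collect emotional distress, self-care behaviors, self-management confidence, interpersonal distress and family conflict by questionnaires that participants complete. For these the participant is the assessor, so masking the data collectors gives no protection. Section 2.2 hypothesises an advantage for the podcast arm on all of them. A reader who trusts the double-blind label would attribute a questionnaire difference to the program, when part of it could come from knowing that one received the richer package.

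**Working it through.** **Comparison of the arms.** This is mainly a matter of setting the sections side by side.

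| Feature | Experimental arm | Control arm | Source |
|---|---|---|---|
| Medium | Audio, 36 episodes | Text e-book | 3.5.1, 3.5.2, Table 3 |
| Interaction | Three personalised voice exchanges with expert reply | None | 3.5.1, Table 3 |
| Prompts to engage | Reminder if episodes not heard | No reminder to read | 3.6.1, 3.5.2 |
| Phone call | At 1.5 months | None during the intervention | Table 3, 3.5.2 |

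The first two rows alone mean that participants know what material they were given. The blinding questions in Section 3.4 record what participants believe about their allocation. They can show that masking failed but cannot supply it.

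**Which outcomes are exposed.**
- Most exposed: emotional distress, self-care, confidence, interpersonal distress and family conflict, all self-rated.
- Less exposed: diabetes knowledge, which is scored on correct answers (3.7.4).
- Within the primary outcome (3.7.2): laboratory HbA1c taken from medical records is the least exposed. The percentage of self-monitored readings in range and the hypo- and hyperglycemic event counts also depend on when and how often participants test.

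**Illustration of size.** The documents give no figure for expectation bias, so the shifts below are assumptions.

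1. Number per arm. Section 3.3.2 gives 38 per group before dropout and a dropout rate of 12%: 38 / (1 − 0.12) = 43.2, rounded up to 44, so 88 in total. This reproduces the plan's figure.
2. Standard error of a difference between two means, in SD units, at one time point: √(2/44) = 0.213.
3. If there is no true effect but expectation shifts the score by δ in favour of the podcast, the chance of a significant two-sided 5% test is P(|Z + δ/SE| > 1.96).

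| Assumed δ (SD) | δ/SE | False-positive rate, 44 per arm |
|---|---|---|
| 0.1 | 0.47 | 7.6% |
| 0.2 | 0.94 | 15.5% |
| 0.3 | 1.41 | 29.1% |

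With the 38 per arm left after the planned dropout, SE = √(2/38) = 0.229 and the same shifts give 7.2%, 14.1% and 25.8%. The planned analysis is a GEE model over four time points, so neither set of figures is the error rate of that analysis.

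**The case against.** The strongest reply is that this is a parallel design in which each participant sees only one product. The e-book has its own title and six diabetes topics, and Section 3.5.2 presents it as a thematically relevant, minimally active control. A participant can know that they have an e-book without knowing that it is the comparator. Arm status is what the Section 3.4 question asks about, and whether participants can infer it depends on what they are told at consent, which is not shown. This part stands: the documents do not prove that participants will identify their arm. But it supports masking to the hypothesis at most, not an unqualified double-blind label.

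The reply can also point out that the questionnaires are already secondary outcomes, that HbA1c is already part of the primary outcome, and that failed masking would be detected. All of this is true, and it limits the damage. It does not correct the label.

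A reader might infer more than the documents support:

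- **Goal setting as an open difference between arms.** HbA1c goal discussions are listed under the experimental heading in 3.5.1. But Table 3 has no such row, and the incentive in 3.6.2 names no arm.
- **No contact with controls.** Table 4 gives both arms field discussion, teach-back and a content checklist. Section 3.5.2 excludes reminders, consultations and follow-up calls, not all contact.
- **Reminders every week.** Section 3.6.1 makes them conditional on not having listened.
- **The device criterion reveals the arm.** Section 3.3.1 gives a rationale ("enabling program transmission and voice interaction for data collection"), but nothing says participants are told it, and an e-book also needs a device.
- **Blinding is claimed as a strength.** Section 4.1 uses the term in its opening sentence. The three strengths it then lists concern theory-based tailored development, voice interaction and treatment fidelity.

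**Conclusion.** The concern holds as a matter of labelling and interpretation. Sections 3.1, 3.4 and 4.1 claim a property that the described arms do not have: participants are not blinded to what they receive and can at most be masked to the hypothesis. Masking of data collectors is described separately and is not in dispute.

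The consequence falls mainly on the five self-rated secondary outcomes. Its size is unknown. The rates of about 8%, 16% and 29% rest on assumed shifts of 0.1 to 0.3 SD and a single-time-point test with 44 per arm. They show how such a bias would act, not that it is present in this trial, and the verdict does not depend on them.

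A reader might go on to conclude that efficacy should be judged on HbA1c alone. The blinding problem does not justify that. Section 3.7.2 defines the primary outcome by four measures, and dropping three of them would change the primary outcome.

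**What to change.** - In Sections 3.1, 3.4 and 4.1, replace the double-blind description with: data-collector-blinded; participants not blinded to the material received, at most masked to the study hypothesis.
- State that emotional distress, self-care behaviors, self-management confidence, interpersonal distress and family conflict are unblinded self-report, open to expectation bias, and to be interpreted as supportive alongside the results of the planned blinding check.
- Add expectation bias to the limitations in Section 4.2.
- Leave the primary outcome definition unchanged, with a note that laboratory HbA1c is its least exposed component.

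The change is to wording and interpretation. Design, sample size and analysis model stay as they are. The downside is the loss of a favourable label.
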